#### Bivariate analysis

The potential advantage of short systemic antibiotics (fewer side effects) versus the potential disadvantage (higher treatment failure rate) will be summarised at the patient level in an advantage score.

The advantage score is defined as the sum of predefined side effect scores at the first two follow-up timepoints: a 1-point increase is equivalent to, in either follow-up period, one level higher for one of each of the five predefined side effects or the presence of either *Clostridium difficile* diarrhoea or intravenous catheter-associated complication. A formal assessment of the difference between the two arms with respect to the advantage score will be based on the difference in mean values with a 95% confidence interval and a *p* value for the test of the null hypothesis of no difference between the treatment groups.

In addition, the difference in mean advantage score and the difference in treatment failure rate will be plotted in a two-dimensional plane together with a 95% confidence region. Furthermore, the ration between the scores will be reported together with a 95% confidence interval. This will allow assessment of the improvement in mean advantage score required for one more treatment failure in 100 patients in order to regard short systemic antibiotic treatment as beneficial. Further secondary analyses are described in Additional file 1.

Data monitoring, interim analysis and criteria for early discontinuation of the study are described in Additional file 1.

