### Sample size

A total of 500 participants will be recruited into this study (250 in each arm). This is based on an anticipated failure rate of up to 13% in the study population overall, 90% power to demonstrate non-inferiority with a non-inferiority margin of 10%. Corresponding simulations indicated a necessary total sample size of 492, rounded up to 500. Deviation from protocol will be accounted for through per-protocol and intention-to-treat analyses conducted in parallel for outcomes relating to infection recurrence.

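### The planned benefit-risk ratio in the bivariate analysis divides by a failure-rate difference the design expects to be zero, so its 95% confidence interval will usually be unbounded; the advantage score is also described inconsistently

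*Protocol article*

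**What the plan says.** The section Bivariate analysis opens by saying that the possible gain from short treatment (fewer side effects) against the possible loss (more failures) "will be summarised at the patient level in an advantage score". It then gives the definition: "The advantage score is defined as the sum of predefined side effect scores at the first two follow-up timepoints". One point is added for each level by which any of five side effects is worse, or for *C. difficile* diarrhoea or an intravenous-catheter complication. Failure does not enter the score.

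Three outputs follow:

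- the difference in mean score, with a 95% confidence interval and a p value;
- a plot of the score difference against the failure-rate difference, with a 95% confidence region;
- a ratio: "the ration between the scores will be reported together with a 95% confidence interval". Its stated use is to judge the "improvement in mean advantage score required for one more treatment failure in 100 patients".

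The section Sample size gives one rate, an "anticipated failure rate of up to 13% in the study population overall", and no separate rates by arm. It reports: "Corresponding simulations indicated a necessary total sample size of 492, rounded up to 500".

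**The concern.** Score improvement per extra failure puts the failure-rate difference in the denominator. If that difference is expected to be zero, the ratio is unstable and a valid 95% confidence set for it is usually not a finite interval. Delta-method or bootstrap limits would be finite, but they would hide the problem.

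The sign is a further difficulty. Take the numerator as long minus short for the score, and the denominator as short minus long for failure. A negative ratio then means either that short treatment is better on both or that it is worse on both, and the ratio alone cannot say which.

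Separately, the description of the score does not match its definition, and its direction is opposite to its name. A reader of the plot or the ratio could easily take an increase for a benefit.

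What is at stake is one secondary summary of the trade-off between side effects and failure. If non-inferiority is shown, this number will rarely have a usable interval.

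**Working it through.** **Inputs.** From Sample size: failure rate 13%, margin 10 points, power 90%, 250 per arm. From Statistical analysis: one-sided test at 0.025. The documents give no mean or standard deviation for the score.

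**Step 1: does the design imply a zero difference?** Take 13% in both arms.

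- Unpooled normal formula: n per arm = (1.960 + 1.282)² × 2 × 0.13 × 0.87 / 0.10² = 10.507 × 0.2262 / 0.01 = 237.7, so 238 per arm and 476 in total.
- Farrington-Manning score test, with restricted rates 0.1947 and 0.0947: [(1.960 × 0.4924 + 1.282 × 0.4756) / 0.10]² = 247.9, so 248 per arm and 496 in total.
- Unpooled power at 246 per arm: SE = √(0.2262/246) = 0.0303; Φ(0.10/0.0303 − 1.96) = 0.91.

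The stated 492 lies between the two totals and within 1% of the score-test figure. A true disadvantage of only 1 point (13.5% v 12.5%) would need 10.507 × (0.1168 + 0.1094) / 0.09² = 293.4, so 294 per arm and 588 in total. At a rate of about 13%, 492 therefore fits equal rates.

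**Step 2: precision of the denominator.** SE = √(2 × 0.13 × 0.87 / 250) = 0.0301, or 3.0 points, and 1.96 SE = 5.9 points.

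**Step 3: how often is the ratio's 95% set unbounded?** By Fieller's criterion the set is bounded only if the denominator differs from zero at the two-sided 5% level. With true difference d and 13% in the long arm, P(unbounded) = 1 − [Φ(d/SE − 1.96) + Φ(−d/SE − 1.96)].

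| True difference (points) | SE (points) | P(unbounded) |
|---|---|---|
| 0 | 3.01 | 95% |
| 1 | 3.06 | 94% |
| 2 | 3.10 | 90% |
| 3 | 3.15 | 84% |
| 5 | 3.23 | 66% |
| 9 | 3.37 | 24% |

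In 200,000 simulated trials with 13% in both arms, the observed difference was exactly zero in about 5%, so the ratio did not exist at all.

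**Step 4: what if the trial succeeds?** A bounded ratio with excess failures on short treatment needs an observed difference above about 5.9 points. Non-inferiority needs one below about 10 − 5.9 = 4.1 points. The two conditions exclude each other, apart from variation in the estimated SE. Together they occurred in at most about 0.001% of simulated trials. Among simulated trials that showed non-inferiority, the ratio was bounded in 2.8%, nearly all with fewer failures on short treatment. A rough check agrees: 0.025 / 0.914 = 2.7%, where 0.914 is the power at 250 per arm.

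This step depends on the rate. The two conditions can overlap once 1.96 SE falls below 5 points, that is when p(1 − p) < (0.05/1.96)² × 125 = 0.0813, or p below about 8.9%. The 95% figure at zero true difference does not depend on the rate.

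**Step 5: the score.** The opening sentence has the score weigh side effects against failure. The definition adds up side effects and complications only, and each added point is a harm. An improvement in mean advantage score must therefore be a decrease.

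**The case against.** The strongest reply is that the ratio is only one of three outputs. The two-dimensional plane puts failure on its own axis, stays valid at zero difference and shows the quadrant, which answers the complaint about sign. All of this stands. A reader might infer that the whole bivariate analysis cannot deliver the trade-off, but the protocol does not support that.

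A reader might also take the missing failure term as the cause of the trouble. It is not. A two-axis analysis needs a score without failure, since including it would count failure twice. The fault lies in the sentence that describes the score. The definition fixes the direction, so the misleading name alone makes no calculation wrong.

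Nor do the documents make the ratio a headline result or a basis for the 10% margin. It appears neither in the abstract nor among the listed secondary objectives. The margin is supported in Statistical analysis by earlier bone-infection studies and by patient representatives' preferences.

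It is also fair to say that the denominator and the zero difference are inferred, and that the interval method may be set out in Additional file 1 or the SAP. The missing method is therefore no fault. But no method gives a valid interval that is reliably finite when the denominator is centred on zero. An unbounded Fieller set is a legitimate result; it just does not supply the figure the section promises.

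Finally, net benefit does not escape every difficulty. The weights at which its interval excludes zero are those outside the Fieller set of the inverted ratio. With an assumed score SD of 2, that set is unbounded in about 61%, 20% and under 0.1% of trials at assumed mean score differences of 0.3, 0.5 and 1.0.

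**Conclusion.** The point holds for the ratio with its interval and for the wording about the score, and no further. Under the design assumption the ratio's valid 95% set is unbounded in about 95% of trials, and still in about 66% at a true difference of 5 points. At 13% failure, a finite interval for the score gain per extra failure almost never coincides with a finding of non-inferiority.

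This rests on three assumptions: the failure-rate difference is the denominator (implied by the stated use), the true rates are equal (implied by 492), and 250 patients per arm contribute. The contradiction about the score rests on the text alone. The mean score difference, the confidence region and the primary conclusion stand as planned. The change is worth making because this section is where the plan sets side effects against failure, and the repair is simple.

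**What to change.** - Keep the plane with its 95% confidence region as the main display.
- Replace the ratio and its interval with NB(k) = k × (mean side-effect score, long minus short) − (failure rate, short minus long), with its 95% confidence interval over a prespecified range of k, where k is the failure proportion accepted per score point. Rearranged, NB(k) is the long-minus-short difference in the mean of (k × score + failure indicator). It is thus an ordinary difference in means that allows for the correlation within patients, and its interval is always finite. State in advance that there may be no k that favours short treatment if the score difference is small.
- If the ratio is kept, define its numerator and denominator, use Fieller sets and report unbounded sets as such.
- Reword the opening sentence to say that side effects and failure are analysed jointly on two axes.
- Rename the score as a side-effect score (higher = worse), and correct ration to ratio.

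The cost is wording in the protocol or SAP, plus prior agreement on the range of k. No new data, visits or patients are needed.

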## Discussion

All investigators involved in the study have acknowledged a position of equipoise in relation to treatment for bone and joint infections; they accept that there is currently insufficient robust clinical evidence defining the optimal duration of systemic antibiotics for management of bone and joint infection.

This study aims to compare the alternative strategies of short and long systemic antibiotic therapy for patients already receiving local antibiotic therapy as part of their standard care for orthopaedic infection. It is recognised that there is heterogeneity within the presenting orthopaedic infection, the local antibiotic therapy used (including antibiotic and carrier properties, dose, site of administration, and resulting local and systemic antimicrobial absorption), the choice and duration of systemic antimicrobial therapy, and the extent of surgical debridement. Nevertheless, randomisation attempts to distribute these contributing factors to treatment effect heterogeneity equally between the groups. This will contribute to the understanding of the validity of alternative systemic treatment strategies in the context of rising adoption of local antibiotic therapy for orthopaedic infection.

## Data Availability

The full datasets generated during the current study will not be publicly available due to the potential for participant self-identification from the data but limited data that would not be identifiable may be published or sought from the senior authors. Reference to protocol items specified in the SPIRIT 2013 Checklist may be found in Additional file 2.

## Abbreviations

CDMS: Clinical Database Management System
DSMB: Data Safety and Monitoring Board
REC: Research Ethics Committee
SAE: Serious adverse event
TSC: Trial Steering Committee
